**Footnotes:**

 Screening visit may be performed on the same day as Visit 1

 Informed consent must be signed prior to initiating any study procedures;

 Randomisation is subjected to vaccine availability;

 Visit 1: third vaccine shot for participant (first and only vaccine administered for the study);

 Physical examination will be done by a qualified study team member or a treating licensed healthcare provider. The physical examination on visit 1 will be conducted during screening prior to vaccination;

 Vital signs include pulse, systolic and diastolic blood pressure, respiratory rate and body temperature prior to vaccination and blood collection;

 For women of child bearing potential a urine pregnancy test will be conducted for Phases A-C of the study, and not for Phase D;

 At each study visit, a review for PCR-confirmed COVID-19 infection will be conducted. In most cases, such information will be available in the participant's HealthHub app. In addition, a review for any positive COVID-19 detected by self-administered Antigen Rapid Test (ART)/supervised self-administered ART/medical professional administered ART will be conducted. For positive results, the category of ART (whether it was self-administered or supervised or administered by a medical professional), the brand of the ART kit used (only if self-administered), and the date of ART positive will be captured;

 All AEs including a list of solicited and other events will be recorded for 7 days after vaccination (see diary version 3.0). Unsolicited AEs will be recorded up to day 28 after vaccination. SAE will be recorded from first vaccination until the end of study period at 12 months. They will be assessed via the listed study procedures, safety laboratory tests, and participant self-recorded diary;

 Safety laboratory bloods will only be monitored during Phases A-C of the study, and not for Phase D

 Haematology tests include full blood count with differential and platelet counts;

 Liver panel includes Albumin, total bilirubin, alkaline phosphatase (ALP), alanine transaminase (ALT); Renal panel includes sodium, potassium and creatinine;

 Cardiology panel include creatine kinase, troponin;

 Blood samples will be collected at NCID research clinic, de-identified/coded before dispatch to local research laboratories such as A\*STAR Singapore Immunology Network and NCID's National Public Health Laboratory. The study team based at NCID research clinic will maintain the codes linking the blood samples to its donor. Subjected to participant consent, any de-identified leftover blood samples may also be analysed for exploratory research to find new scientific information about coronaviruses and related diseases, which may occur locally or overseas;

 Blood sample for immunogenic studies may be taken at Visit 1 instead of Screening if the blood draw is not possible for one reason or another. The study team will make every effort to complete all blood-taking in one seating to avoid pricking the participants more than once.

## 5. STUDY DESIGN

### 5.1. Summary of Study Design

PRIBIVAC is an adaptive, randomised, subject-blinded, controlled trial to assess the immunogenicity and safety of heterologous boost COVID-19 vaccination (intervention groups) compared with a homologous boost regimen (control group). For phases A-C of the study potential participants would have already received the second dose of a homologous prime-boost vaccination with BNT162b2 or mRNA-1273 at least six months prior to enrolment. For Phase D a booster dose of either BNT162b2 or mRNA-1273 would have been administered at least five months prior to enrolment.

In Phase A-C of the study the booster vaccine for the control arm will be the homologous mRNA vaccine (e.g. BNT162b2 + BNT162b2 + BNT162b2 or mRNA-1273 + mRNA-1273 + mRNA-1273), while for individuals randomised to intervention group 1 the mRNA booster vaccine administered will be heterologous to the primary series (e.g. BNT162b2 + BNT162b2 + mRNA-1273 or mRNA-1273 + mRNA-1273 + BNT162b2). The booster vaccine candidates for intervention groups 2 and 3 were an alternative COVID-19 vaccine.

Control group: Homologous mRNA booster vaccine

Intervention group 1: Heterologous mRNA booster vaccine

Intervention group 2: Non-mRNA booster vaccine A (i.e. COVAXIN®)

Intervention group 3: Non-mRNA booster vaccine B (i.e. Nuvaxovid)

Phase D of the study will examine the immune response following a second COVID-19 vaccine booster. Study participant will be randomised to receive one of three vaccines in equal proportions: Comirnaty or Comirnaty Bivalent (Original/Omicron BA.4/5), Moderna/Spikevax or Moderna/Spikevax Bivalent (Original/Omicron BA.1) or Nuvaxovid. Vaccines are obtained from the Singapore Ministry of Health stockpile. Where possible the bivalent Comirnaty/Spikevax vaccines will be administered to study participants, however, because of uncertainties in availability the monovalent may be administered if bivalent stock is not available in Singapore. For analysis the reference point for determining homologous and heterologous vaccination regimen may include the primary vaccine series or first booster.

COVID-19 vaccines used in the study may have been granted full or interim authorisation (under the Pandemic Special Access Route, PSAR) by the Health Sciences Authority (HSA), have been authorised via the Special Access Route (SAR) for vaccines as part of the Emergency Use List (EUL) of the World Health Organization (WHO), or be under clinical development. BNT162b2, mRNA-1273 were authorised in Singapore under the PSAR, and on 3 Feb, HSA granted interim authorisation for Novavax's vaccine-manufactured under the name Nuvaxovid under PSAR. Nuvaxovid became the first non-mRNA vaccine accepted as an alternative for a boost vaccination in Singapore. Comirnaty Bivalent (Original/Omicron BA.4/5) and Moderna/Spikevax Bivalent (Original/Omicron BA.1) were authorised in Singapore under the PSAR on 11 Oct 2022 and 14 Sept 2022 respectively for use as a booster vaccine.

The non-mRNA vaccine COVAXIN® (Bharat Biotech) was approved by the World Health Organization (WHO) under the Emergency Use Listing (EUL) procedure on 3 Nov 2021 for use in two doses for primary vaccination and is available in Singapore via the SAR. The booster is not approved in the EUL.

Participants will be enrolled at the NCID research clinic. Participants will be blinded to the vaccine allocation (study team will not be blinded) to reduce the risk of bias in self-reported AEs. Participants will receive the blinded vaccination on study day 0 / visit 1. Participants will be observed for 30 minutes in the clinic after vaccination as per standard clinical practice. Participants will be monitored and followed up for AEs at Day 28 and SAEs throughout the study by physical examinations, laboratory tests and self-reporting. Blood samples will also be taken during screening or day 0, and at the follow-up visits at days 7, 28, 180, 360 post-enrolment for evaluation of immunogenicity and/or safety. Any missed follow-up visits by participants will not be considered a protocol deviation as it is beyond the control of the study team if a participant does not turn up for a follow-up visit, especially in a large-scale study.

For Phase A-C because of limited available data and the potential for inclusion of vaccines which were not approved as a booster, safety and futility was reviewed by an independent data and safety monitoring board (DSMB) after the first 10 participants in each of the intervention arms had completed assessments at study day 28. The DSMB was in a position to recommend discontinuation of a study arm on the basis of safety concerns or futility in immunogenicity. An outline of this safety monitoring plan is provided in Section 9.4 and more details will be provided in the DSMB charter.

For Phase D of the study we will study only COVID-19 vaccines approved for use by HSA. As such a DSMB will not be convened.

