Since the first detection of the XBB Omicron subvariant in August 2022 in India, it has been detected in more than 17 countries to-date including Singapore, Australia, Bangladesh, Denmark, Japan and the US. The current wave of COVID-19 cases in Singapore, driven by the XBB strain, is expected to peak in mid-November 2022 with about 15,000 daily cases on average. The proportion of reinfections among total COVID-19 cases in Singapore is also on the rise, currently making up about 17% of total new cases. To combat the rising COVID-19 infections and reinfections, the bivalent Moderna/Spikevax vaccine was added to the National Vaccination Programme from 14 October 2022 for persons who have yet to achieve minimum protection (i.e. received at least 3 doses of mRNA/Nuvaxovid or 4 doses of Sinovac-Coronavac), or those aged 50 years and above who have received their last vaccine dose more than five months ago. On 25 October 2022, Singapore's HSA granted interim authorisation of a booster dose of the Pfizer-BioNTech bivalent vaccine for individuals aged 12 years and older.

From 14 Nov 2022, a second booster dose from five months to one year after the last vaccine dose is recommended by MOH for all individuals aged 18 years or older.

The updated bivalent vaccine is preferred for this. A person is considered up-to-date with their COVID-19 vaccination if they have received at least the minimum protection and their last vaccine dose was received within the past one year. The bivalent Moderna/Spikevax vaccine is currently available, and the bivalent Pfizer-BioNTech vaccine is expected to be available by the end of this year.

PRIBIVAC will assess a heterologous prime-boost-boost strategy in comparison with a homologous regimen in order to compare short and long-term immunogenicity of different COVID-19 vaccine combinations against the ancestral SARS-CoV-2 as well as different VOCs. Initial phases of the study have studied homologous versus heterologous vaccines at the first booster, later phases will study these as the second booster.

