## **6. METHODS AND ASSESSMENTS**

### **6.1. Randomisation and Blinding**

Randomisation will be performed using a web-based randomisation system hosted by Singapore Clinical Research Institute (SCRI), in which a randomisation list with randomised permuted blocks will be generated by the trial statistician. Password secured accounts will be assigned to the site personnel who are responsible for the randomisation, where he/she can log into the randomisation system using the Internet.

For the first booster part of the trial randomisation will be stratified by the following criteria:

1. Age (<60, ≥60)
2. Primary vaccine series (BNT162b2 or mRNA-1273)
3. Time from 2nd vaccine dose administered (6-9 months, >9 months)

For the second booster part of the trial randomisation will be stratified by the following criteria:

1. Age (<60, ≥60)
2. Primary vaccine series (BNT162b2 or mRNA-1273)
3. First booster vaccine received (BNT162b2 or mRNA-1273)

Eligible participants will be randomised in equal proportions to each of the study arms that are open for randomisation. Enrolment to a study arm will be discontinued if recommended by DSMB or if the target sample size of 100 in the study arm has been reached. In the scenario where recruitment is discontinued in any of the intervention arms from 1 to 4 at the interim analysis, randomisation to the control arm may continue beyond 100 participants until the target sample size of 100 participants has been reached in the remaining intervention arms.

Allocation concealment will be maintained until the registration and randomisation process have been completed. For Phase A-D of the study, vaccine allocation will be single-blind, i.e. only participants will be blinded. Blinding will be maintained for the participants till their Day-28 Visits (Visit 3).

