## **11. SAMPLE SIZE AND STATISTICAL METHODS**

### **11.1. Determination of Sample Size**

Based on the data from our ongoing COVID-19 vaccine immune-monitoring study (SCOPE), the mean level of SARS-CoV-2 anti-spike immunoglobulins was 84% (SD=15%) at 28 days after the second dose. This was determined using a SARS-CoV-2 surrogate virus neutralisation test (sVNT) that detects total immuno-dominant neutralising antibodies targeting the viral spike (S) protein receptor-binding domain in an isotype- and species-independent manner. We expect immunogenicity will be boosted back to the same level after the booster dose in the control arm. With an assumed immunogenicity level of 81% in an intervention arm and a non-inferiority margin of -10%, a sample size of 87 subjects per arm will ensure concluding non-inferiority of the intervention arm against the control arm with 80% power. The sample size is calculated at a one-sided 2.5% significance level and allows for a 15% dropouts. A sample size will offer power of 85.1% based on the above parameters.

Since recruitment of subjects to intervention arms may be activated in a staggered way depending on availability of the vaccines, and recruitment to the control arm will continue until the target

sample size of 100 is achieved in each intervention arm, we prepare to enrol a double sample size in the control arm for the purpose of study planning. This gives a total sample size of up to 600 subjects.

For Phase D of the study, the objective is to estimate the mean difference in humoral immunity (log10-transformed anti-S at day 28) between Pfizer vs Moderna, Pfizer vs Nuvaxovid and Moderna vs Nuvaxovid received as 2nd booster (three mean difference estimations). No hypothesis testing will be performed.

The standard deviation of day 28 log10-transformed anti-S titre from Phase A of the study was assumed to apply to responses to the second booster (note data from those aged 60 years and above per current MOH advisory for a second COVID-19 booster). Using confidence interval approach for sample size calculation, a sample size of 50 per arm (after allowing 5% dropout rate) was estimated to produce two-sided 95% confidence interval with distance from difference in means to limits that is equal to 0.13 when standard deviation of log10-transformed anti-S titre is assumed to be 0.32 for both arms that is being compared.

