### *c. Efficacy Analyses*

Graphical plots will be produced for the various immunity endpoints to depict the change of immunity levels over time. Levels of SARS-CoV-2 anti-spike immunoglobulins will be summarized by study arm and by randomisation stratification factors. Mean difference and its 95% CI in levels of SARS-CoV-2 anti-spike immunoglobulins between an intervention arm and the control arm (for Phase A-C), and between pairwise arms (for Phase D) will be estimated from a general linear regression model which adjusts for level of SARS-CoV-2 anti-spike immunoglobulins at baseline, and randomisation stratification factors. If the lower bound of the 95% CI of Phase A-C SARS-CoV-2 anti-spike immunoglobulins falls above -10% (the pre-specified non-inferiority margin), non-inferiority of the intervention arm will be concluded. For Phase D, reported mean differences and 95% CIs are exploratory in nature. Analysis of repeated measurements of immunity endpoints will be performed with the use of mixed effects models that adjust for baseline values and randomisation stratification factors. Log-transformation of the data may be applied as needed before the analyses.

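### Phase D names its contrasts by manufacturer, but each mRNA arm mixes monovalent and bivalent vaccine by stock, so the pooled estimates are brand-as-supplied effects and need formulation-specific companions

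*Protocol*

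**What the plan says.** **Arms.** Protocol 5.1: "Study participant will be randomised to receive one of three vaccines in equal proportions". The three are Comirnaty or its bivalent (Original/Omicron BA.4/5), Spikevax or its bivalent (Original/Omicron BA.1), and Nuvaxovid. The bivalent is preferred, but "because of uncertainties in availability the monovalent may be administered if bivalent stock is not available in Singapore". Formulation is therefore set by national stock and is not randomised.

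**Contrasts.** Protocol 11.1 sets out three mean differences in log10 anti-S at Day 28: "Pfizer vs Moderna, Pfizer vs Nuvaxovid and Moderna vs Nuvaxovid". Formulation does not enter.

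**Model.** Protocol 11.2 c uses a "general linear regression model which adjusts for level of SARS-CoV-2 anti-spike immunoglobulins at baseline, and randomisation stratification factors". Under 6.1 the second-booster strata are age, primary series and first booster vaccine. Neither formulation nor enrolment period is among them.

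**Supply.** Protocol 1.2 a: "The bivalent Moderna/Spikevax vaccine is currently available, and the bivalent Pfizer-BioNTech vaccine is expected to be available by the end of this year". The same section dates the entry of bivalent Moderna into the national programme to 14 October 2022. Section 3.1 gives a recruitment period of one year.

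**Status.** Sections 11.1 and 11.2 c make Phase D an estimation exercise without hypothesis tests, with exploratory intervals.

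**The concern.** The arms, the contrasts and the model do not fit together. Each mRNA arm can contain two products, while the contrast carries a single manufacturer's name. In the supply window that section 1.2 a describes, the rule in 5.1 would give monovalent vaccine to the Pfizer arm and bivalent to the Moderna arm. Once both bivalents are in stock, both arms receive bivalent.

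The pooled Pfizer-Moderna estimate then averages two different product comparisons, weighted by how many participants happened to enrol in each period. The Pfizer-Nuvaxovid and Moderna-Nuvaxovid estimates inherit the same mixture. Section 1.2 a also reports that a Moderna bivalent gave better Omicron neutralisation than the monovalent, so the protocol does not itself treat the formulations as interchangeable.

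At stake is interpretation. Estimating these differences is the stated aim of Phase D, and a reader would naturally take a result headed Pfizer versus Moderna as a property of two vaccines. In part it would reflect supply.

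**Working it through.** **1. The plan's own precision.** Inputs from 11.1: SD 0.32 log10 in both arms, half-width 0.13, two-sided 95%, 5% dropout.

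- n = 2 × (1.96 × 0.32 / 0.13)² = 46.6, so 47 evaluable per arm.
- 47 / 0.95 = 49.5, so 50 per arm, as stated.
- Half-width with 47 per arm: 1.96 × 0.32 × √(2/47) = 0.129.

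The sample-size arithmetic is sound. Section 3.1 plans 250 participants. Split three ways less 5%, that is 250/3 × 0.95 = 79 evaluable per arm, with half-width 1.96 × 0.32 × √(2/79) = 0.100.

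**2. What pooling does.** Let p be the proportion of an arm that received bivalent vaccine, and g the bivalent-minus-monovalent difference in log10 anti-S, taken as equal for both brands for illustration. Relative to a comparison at equal formulation mix, the Moderna-Pfizer difference moves by

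shift = (p_Moderna − p_Pfizer) × g.

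Relative to a wholly monovalent comparison, each mRNA-Nuvaxovid difference moves by p × g for that arm.

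**3. Inputs that the protocol does not give.**

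- g for anti-S is not stated. Assumed range: 0.10 to 0.25 log10, a titre ratio of about 1.26 to 1.78.
- The difference in bivalent shares is not stated. From 14 October to 31 December 2022 is 78 days, and 78/365 = 21%. So if enrolment were even over a year containing that whole window, and supply came as forecast, the shares would differ by about 20 points. Clustered enrolment or late supply could raise this; 50 points is taken as a less favourable case.

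| Difference in bivalent shares | g = 0.10 | g = 0.25 |
|---|---|---|
| 20 points | 0.20 × 0.10 = 0.02 | 0.20 × 0.25 = 0.05 |
| 50 points | 0.50 × 0.10 = 0.05 | 0.50 × 0.25 = 0.125 |

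Against the planned 0.13, the 20-point row is 15% to 38% of the half-width and the 50-point row 38% to 96%.

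**4. Whether a covariate would repair it.** Arms open together are randomised concurrently, so stock period is balanced between them. A main effect for period therefore leaves the arm difference essentially unchanged. A formulation term is nested within arm, and where Pfizer is all monovalent and Moderna all bivalent it is aliased with arm. Only a period-by-arm interaction or separate contrasts by period can separate the comparisons.

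**5. Precision of a contrast limited to the both-bivalent period.** With 79 evaluable per arm and a fraction f of enrolment in that period (assumed), the half-width is 1.96 × 0.32 × √(2/(79f)):

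- f = 75%: 0.115
- f = 50%: 0.141

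**The case against.** The strongest defence is that randomisation is intact. Section 6.1 allocates equally among the arms open at the time, so enrolment date is balanced between arms open together. The pooled difference is then an unbiased estimate of a policy that 5.1 states openly: this brand, bivalent where possible, otherwise monovalent. This stands. A reader might infer that the brand difference is spurious or confounded by calendar time; the documents do not support that. Enrolment date decides which formulation an arm gives, but it does not by itself bias the comparison of concurrent arms.

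It can also be said that the superiority reported in 1.2 a concerns Omicron neutralisation for one Moderna bivalent, whereas the Phase D quantity in 11.1 is anti-S, and that the section describes the Comirnaty Bivalent trials as still under way. This stands too: the size of any anti-S effect is unknown. Nor does the protocol say how many Phase D participants were randomised in the mismatched window. Section 5.1 says only that monovalent may be given, and the schedule in section 4 makes randomisation depend on vaccine availability.

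Finally, Phase D is exploratory, and an analysis plan not seen here might break results down by formulation. The first part limits the severity. The second does not remove the point, because the protocol itself fixes the contrasts by manufacturer and names the covariates.

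**Conclusion.** The point holds as one of interpretation. For arms open together, the pooled Phase D estimates are valid randomised brand-as-supplied effects, but their meaning depends on an uncontrolled formulation mix, and neither the contrasts nor the model separates the formulations.

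The size cannot be fixed from the protocol. Under the assumed bivalent effect of 0.10 to 0.25 log10, the shift is about 0.02 to 0.05 log10 if supply came as forecast and enrolment was even, and 0.05 to 0.125 if the shares differ by 50 points. A reader might infer that the distortion rivals the planned half-width of 0.13. That is so only at the upper end of the less favourable case, and both of its inputs are assumptions. If nearly everyone enrolled while both bivalents were in stock, the effect would be small.

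Severity is minor: no test or decision rule depends on it. The change is a cheap improvement.

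**What to change.** In Protocol 11.1 and 11.2 c:

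1. Keep the pooled pairwise contrasts, but label them brand-as-supplied.
2. Add contrasts by product and formulation among participants randomised concurrently in the same stock period. For example, compare Comirnaty Bivalent BA.4/5, Spikevax Bivalent BA.1 and Nuvaxovid while both bivalents were in stock, and treat other periods as separate strata. These comparisons stay randomised.
3. Name these contrasts by product. The two bivalents target different Omicron lineages, so even this comparison does not isolate brand.
4. If one model is preferred, include a period-by-arm interaction; a main effect for period is not enough.
5. Report the formulation mix per arm.
6. Confirm that the trial database holds the formulation given. Section 10.2 lists arm allocation, and 8.5 sends vaccination details to the national immunisation record; neither shows that formulation is captured for analysis.

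**Cost.** A change of analysis wording and a check of the data fields. The price is precision: with 79 evaluable per arm, the half-width goes from 0.100 to about 0.115 if 75% of enrolment falls in the both-bivalent period and to 0.141 if 50% does. Those shares are assumed.
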